[figure not shown]

## 1. Abstract:

**Background:** Type 2 diabetes mellitus (T2DM) and related non-communicable diseases (NCDs) are significant public health challenges in Bangladesh, with a high prevalence among adults. Culturally tailored, faith-based interventions led by religious leaders have shown promise in promoting healthy behaviors and preventing T2DM. This study will evaluate the effectiveness of a faith-based lifestyle intervention delivered by mosque imams in reducing T2DM incidence and improving cardiometabolic outcomes among high-risk individuals in rural Bangladesh.

**Objectives:** The primary objective will be to assess the impact of a faith-based lifestyle intervention on the incidence of T2DM among high-risk individuals with prediabetes. Secondary objectives will include evaluating changes in cardiometabolic parameters, quality of life, and diabetes-related knowledge.

**Design:** A cluster-randomized controlled trial (RCT) will be conducted across eight mosques in rural Bangladesh. Mosques will be randomly assigned to either the intervention or control group. The intervention will consist of religious sermons promoting healthy behaviors, dietary guidance, and physical activity, while the control group will receive standard health education.

**Study areas:** The study will be conducted in eight mosques located in the districts of Manikganj, Narshingdi, Munshigonj, Dhaka, and Tangail. Four mosques will serve as intervention sites (Shibaloy, Monohardi, Raipura, and Dhanbari), and four will serve as control sites (Singair, Keraniganj, Sreenagar, and Sakhipur).

**Study duration:** 12 months (April 2022 to April 2023).

**Target population:** A total of 824 participants aged 25–65 years with prediabetes (based on WHO criteria) will be enrolled. Participants will be permanent residents of the study areas and willing to participate for the entire study duration.

**Statistical analysis:** The primary outcome will be the cumulative incidence of T2DM at 12 months. Secondary outcomes will include changes in weight, body mass index (BMI), blood pressure, blood glucose, lipid profiles, and quality of life. Data will be analyzed using intention-to-treat analysis, with comparisons between groups made using chi-square tests, t-tests, and mixed-effects models.

**Conclusion:** This study will provide evidence on the effectiveness of a faith-based lifestyle intervention in preventing T2DM and improving cardiometabolic health in a low-resource setting. The findings will inform scalable and culturally relevant strategies for diabetes prevention in Bangladesh and similar contexts.

**Keywords:**

Diabetes prevention, faith-based intervention, religious leaders, lifestyle modification, Bangladesh.

**Study Coordination:** Diabetic Association of Bangladesh.

## 2. Background

Diabetes (T2DM) is now considered a significant public health burden in Bangladesh. International Diabetes Federation (IDF) reported that 13.1 million people living in Bangladesh had T2DM in 2021, and of them, 43% were unaware of their diabetes (T2DM) status [1]. Bangladesh at present is in the 8th position in the world by the total number of people with T2DM. Older age, affluent socioeconomic status, carbohydrate-rich foods, physical inactivity, obesity, smoking, HTN, dyslipidemia, increased age at pregnancy, and depression are significant risk factors for T2DM [2-4]. Studies have also shown that people with T2DM in Bangladesh receive two times more inpatient treatment days and require one and half times more outpatient visits and more than nine times more medications than normal individuals [5]. Overall, a person with T2DM in Bangladesh spends nine percent of their annual household income managing the disease. The total annual per capita expenditure on medical care is six times higher for people with T2DMs (US\$635 vs. US\$104, respectively). Using productivity-adjusted life years (PALY), it is projected that more than nine million PALYs (20.4%) are attributable to having T2DM. In Bangladesh, the loss in PALYs linked to a total of US\$97.4 billion lost (US\$16 987 per person) in gross domestic product [6, 7].

T2DM is a complex metabolic disorder. Before diagnosis, it normally passes through a prolonged dormant period and remains untreated. Studies have shown that approximately 30–50% of people with T2DM usually presented with one or more micro- or macrovascular complications at the time of diagnosis [8-10]. For these reasons, early identification of people with undiagnosed T2DM or those at an increased risk for developing T2DM has been recommended to improve outcomes. Several randomized clinical trials have also shown that lifestyle intervention strategies can prevent and delay the progression of T2DM among high-risk individuals, which is highly cost-effective [11-15].

The majority of people (89%) in Bangladesh are Muslim. Mosques are the common meeting place for adult Muslims in Bangladesh, and religious leaders (Mosque Imams) are respected and influential figures in the Muslim community. People seek advice from the Mosque Imams about all sorts of matters and trust them with personal and family matters. Not only that, in the Islamic tradition, a religious sermon (Khutbah) serves to deliver words of exhortation, instruction, or command at gatherings for worship in the mosque at weekly (congregation prayer on Friday) and annual (Eid) rituals. Powerful messages on a healthy lifestyle already exist in Islam. Therefore, there is a wonderful opportunity to seek the influence of Imams in creating community awareness about the prevention of T2DM and other NCDs and helping educate people to take proactive action and change their lifestyles. To date, we have not estimated the value that could be gained from investing in faith-based lifestyle interventions targeting the adult Bangladeshi population.

To address this gap in the evidence and inform decision-making for T2DM prevention among the Bangladeshi population, this study will evaluate the effect of faith-based (religious leaders) lifestyle intervention to prevent T2DM in high-risk individuals using a prospective randomized control study design.

### **3. Diabetes Prevention through Religious Leaders (DPRL) [16]**

Considering the influence of religious leaders, BADAS has started a prevention program, “Prevention of Diabetes through Religious Leaders,” for the last three years to improve community awareness of a healthy lifestyle for prevention and care of diabetes and other NCDs through religious leaders. Initially, it was funded by World Diabetes Foundation. It is now a joint community awareness program of BADAS, the Islamic Foundation of Bangladesh (Ministry of Religious Affairs), and the Non-Communicable Disease Control (NCDC) program of DG Health (Ministry of Health and Family Welfare).

100 Masque Imams from 100 Upazilas of Dhaka and Mymensingh division received training, and BADAS has already established 100 diabetes corners in their Mosques. Besides Friday Sermon, Mosque Imams usually check blood glucose, blood pressure, anthropometric measurement and provide basic education on a healthy lifestyle to prevent T2DM and related diseases in their diabetes corners. They also charge 40 BDT for using the health package. As part of the program, Each Imam has a female assistant (she may be his wife, sister, daughter, or any woman appointed by the local Mosque committee) for improving female participation in their community. About 30000 people have already taken care of these centers. Islamic Foundation, Ministry of Religious Affairs; Non-communicable Disease Control program of DG Health, Ministry of Health and Family Affairs; National Mosque of Bangladesh, Bangladesh Madrasah Education Board, and Befaqul Madarishil Arabia Bangladesh have approved this program, and the religious sermon (Khutbah) for its nationwide application. Islamic Foundation has also given written instruction to three lacs registered mosques throughout the country for using this Khutbah for creating community awareness on a healthy lifestyle. Besides these, a total of 100000 Mosque Imams received the printed Khutbah for building community awareness. It is now the biggest platform for creating community awareness on a healthy lifestyle to prevent diabetes and related NCDs.

### **4. Rationale of the study**

Like other South Asian (SA) countries, Bangladesh is also facing an increased health challenge associated with rapid economic transition, migration from traditional rural to more urban locations, and changes in their dietary and physical activity practices [17-19]. An increased predisposition to non-communicable diseases (NCDs) is an adverse consequence of these changes, with increased prevalence of obesity and central adiposity leading to an increased risk of T2DM. The Government of Bangladesh has adopted the WHO Global Action Plan for the Prevention and Control of NCDs 2013–2020, and they have further committed to universal health coverage (UHC) by 2030. Although the country has a national action plan for facing the epidemiological transitions of T2DM, countrywide implications have received less attention.

Early identification of people with undiagnosed T2DM or those at an increased risk for developing T2DM has been recommended to improve outcomes. Several randomized clinical trials have also shown that lifestyle intervention strategies can prevent and delay the progression of T2DM among high-risk individuals, which is highly cost-effective. One Bangladeshi study showed that overall, US\$297 could be saved annually by

preventing only one case of T2DM [20]. The Government should prioritize T2DM prevention and control programs, such as creating mass awareness and changing lifestyle habits through well-designed public health programs.

The majority of people (89%) in Bangladesh are Muslim. Mosques are the common meeting place for adult Muslims in Bangladesh, and religious leaders (Mosque Imams) are respected and influential figures in the Muslim community. People seek advice from the Mosque Imams about matters and trust them with personal and family issues. Not only that, in the Islamic tradition, a religious sermon (Khutbah) serves to deliver words of exhortation, instruction, or command at gatherings for worship in the mosque at weekly (congregation prayer on Friday) and annual (Eid) rituals. Along with religious issues, religious leaders also provide solutions for the different problems arising in society through Khutbah. Powerful messages on a healthy lifestyle already exist in Islam. Therefore, there is a wonderful opportunity to seek the influence of Mosque Imams in creating community awareness about preventing T2DM and other NCDs and helping educate people to take proactive action and change their lifestyles.

In Bangladesh, the Diabetic Association of Bangladesh (BADAS) has successfully included religious leaders to influence the improvement of community awareness about the prevention of T2DM - "Diabetes Prevention through Religious Leaders" and the prevention of GDM and future T2DM "Preconception Care through Religious Leaders" [16, 21]. The Bangladesh DMagic trial reported that community mobilization using the participatory learning and action (PLA) approach improved knowledge and awareness about T2DM and significantly lowered the prevalence of T2DM and intermediate hyperglycemia [22]. Therefore, it is vital to estimate the effectiveness of faith-based lifestyle interventions targeting the adult Bangladeshi population for policy implications and design suitable preventive interventions. Data on the current state of T2DM and its prevention in rural areas is also important because about 62.6% of the total population lives in rural communities of Bangladesh.

## **5. Literature review: (will describe the previous and ongoing works related to this study)**

We searched PubMed, CINAHL, EMBASE, Web of Science, and Google Scholar for systematic reviews and published original studies published up to May 2021, with a particular focus on lifestyle intervention for the prevention of T2DM through Religious Leaders in low and middle-income countries. We used the search terms "T2DM", "diabetes prevention," "lifestyle interventions," "religious leaders," "peer education," and "community participation." There were no language restrictions used. Because we wanted to understand both the nature of existing interventions and their effectiveness, we were interested in a range of studies, including systemic reviews, randomized controlled trials, pilot studies, and case-control studies.

Good evidence exists for group support, and peers support lifestyle interventions to prevent or delay the onset of T2DM [22]. Evidence supports community and peers' involvement as a cost-effective means of promoting lifestyle changes in high-income settings, but research in resource-poor settings is lacking. Evidence on the

effects of community mobilization on T2DM and related risk factors among the general population, as opposed to high-risk individuals, is yet to emerge from low-income or middle-income countries.

Several recent efforts to reach high-risk populations, such as African Americans, have focused on delivering lifestyle interventions through faith-based institutions (FBO) [23, 24]. Findings indicate FBOs may be a promising avenue for providing diabetes self-management education (DSME) to Black Americans. Informed by the results, a focused discussion on advancing the science of faith-based interventions to expand the delivery of DSME to Black Americans with T2DM is provided [25-27].

Studies have shown that Islamic religious leaders (IRLs) can influence health education, health promotion, and positive health outcomes among their communities. They have played a significant role in creating public awareness of reproductive health, HIV/AIDS, immunization, and family planning and played an important role in paving the way for promoting a healthy lifestyle [28-29]. Religious decrees (fatwa) issued by Muslim scholars guide diabetic patients in various fields from Insulin injection, other medications, fasting in Ramadan, and even novel treatments such as therapeutic use of stem cells.

Study findings reveal that 1) culturally sensitive, behaviorally oriented interventions incorporating social support are needed to achieve positive health outcomes. Findings indicate FBOs may be a promising avenue for delivering DSME, 2) IRLs are effective social agents for change, and that the educational interventions can be a useful and effective strategy to encourage IRLs to cooperate with health providers and promote public health among their communities and 3) religion should be explored as a potential tool to reach out on facts while doing away with erroneous beliefs about T2DM.

## **6. Hypothesis:**

- A faith-based lifestyle intervention delivered by mosque imams will significantly reduce the incidence of type 2 diabetes mellitus (T2DM) among high-risk individuals with prediabetes in rural Bangladesh over a 12-month period, compared to a control group receiving standard health education.

## **7. Research questions:**

- Does a faith-based lifestyle intervention delivered by mosque imams reduce the incidence of type 2 diabetes mellitus (T2DM) among high-risk individuals with prediabetes in rural Bangladesh over a 12-month period, compared to a control group receiving standard health education?

## **8. Objective:**

### **8.1 Primary objectives:**

- To evaluate the effectiveness of a faith-based lifestyle intervention in reducing the incidence of T2DM among high-risk individuals with prediabetes over a 12-month period.

### **8.2. Secondary objective:**

- To assess changes in cardiometabolic parameters, including weight, BMI, blood pressure, blood glucose, and lipid profiles.

- To assess changes in dietary habits and physical activity levels.
- To evaluate improvements in quality of life and diabetes-related knowledge among participants.
- To determine the cost-effectiveness of the intervention.

## 9. Outcome Indicators

### 9.1 Primary outcomes:

- Cumulative incidence of T2DM at 12 months.

### 9.2 Secondary outcomes

- Changes in cardiometabolic risk factors (weight, BMI, BP, lipid profile, glycaemic control).
- Improvements in diabetes knowledge and self-care behaviors.
- Changes in physical activity and dietary habits.
- Cost-effectiveness assessment.

## 10. Research methodology

### 10.1 Study design and participants

This cluster-randomized controlled trial (RCT) will be conducted across eight mosques in rural villages of five districts in Bangladesh: Manikganj, Narshingdi, Munshigonj, Dhaka, and Tangail. The study will target rural areas to address the unique challenges faced by these communities. Participants will be randomly allocated to either the intervention or control group at the cluster level (mosques). Eight mosques will be selected using a simple random procedure, with four assigned to the intervention group and four to the control group. Mosques will be randomly assigned as intervention or control sites using block randomization to ensure geographic diversity and balance across groups. Randomization lists will be generated centrally and concealed from field teams to minimize bias. Intervention centers will be in Shibaloy, Monohardi, Raipura, and Dhanbari, while control centers will be in Singair, Keraniganj, Sreenagar, and Sakhipur. All mosques are recognized by the Islamic Foundation of the Ministry of Religious Affairs and have an education center for learning the Holy Quran.

Participants will be recruited using the most recent voter list and age distribution data for Bangladesh. Each site will have an estimated population of 2,500 to 3,000 individuals, from which 1,500 individuals aged 25 to 65 years will be invited to participate. According to Bangladesh's age distribution, 45–47% of the population falls within this age group [30, 31]. The target recruitment goal is to enroll up to 108 participants from each mosque.

Recruitment will initiate at each mosque 4 weeks before the introduction of the intervention. The Imams will discuss and convey the message of a healthy lifestyle including diet and exercise during the Friday sermon and use a standardized script to encourage congregational participation in practice. They will distribute investigator-developed flyers to congregational participants to promote the study objectives. They will also discuss the importance of female participation as part of the intervention. Members of the research team will also attend Friday sermons to assist with recruitment and provide information regarding the study.

Any men and non-pregnant women aged 25 years and older with an individual's diabetes risk score  $\geq 9$  and diagnosed prediabetes (IFG/IGT) as per WHO recommended diagnostic value will be the units of analysis. Project members will use the DPRL diabetes corner situated near the mosque for the screening, intervention, and further follow-up of male participants. For females, project members will use a house nearby the selected mosques. We will use an Imam's woman assistant in each center for the requirements of women participants.

**10.2 Study period:** 12 months (April 2022 to April 2023).

### **10.3 Inclusion Criteria**

- All individuals aged 25-65 years with diabetes risk score  $\geq 9$  [32] and diagnosed with prediabetes (IFG/IGT) as per WHO recommended diagnostic value [33]. These are the primary inclusion criteria.
- Both Gender
- Permanent residents
- Willing to participate and available for 12 months of study

### **10.4 Exclusion criteria**

- Pregnant women or planned pregnancy and lactating mothers
- Known case of T2DM
- Individual diagnosed with acute physical or mental illness at the time of screening

### **10.5 Study variables**

- **Socio-demographic variables:** age, sex, economic status, education status, smoking habit, lifestyle (physical activity and food habit).
- **Anthropometric variables:** height, weight, body mass index (BMI), waist circumferences (WC), waist-height ratio (WHR), and waist-height ratio (WHtR).
- **Clinical & Biochemical variables:** blood pressure, fasting blood glucose (FBG), 2-hour blood glucose, HbA1c, fasting lipid profile, ECG and fundus photography.
- **Quality of Life:** Assessed using the EuroQol-5D-5L scale and EuroQol-VAS score.
- **Diabetes Knowledge:** Assessed through structured questionnaires.
- **Economic Variables:** employment status, productivity loss (income and days/hours of work lost), out-of-pocket payments (OPP), the opportunity cost of time (average wage and time), borrowing/selling assets, expenditure.

### **10.6. Size of the study population and power calculation**

The sample size for this cluster-randomized controlled trial (RCT) was calculated to detect a 50% reduction in the incidence of type 2 diabetes mellitus (T2DM) in the intervention group compared to the control group. This assumption was based on evidence from previous landmark lifestyle intervention trials, such as the Diabetes Prevention Program (DPP) in the United States and the Finnish Diabetes Prevention Study (DPS), which reported a 58% reduction in T2DM risk among high-risk individuals.

#### **Key Parameters for Sample Size Calculation:**

1. Primary Outcome: A 50% reduction in T2DM incidence in the intervention group compared to the control group.

2. Power: 80% power to detect the effect.
3. Significance Level: 5% ( $\alpha = 0.05$ ).
4. Intraclass Correlation Coefficient (ICC): 0.05 to account for clustering within mosques.
5. Dropout Rate: 50% to account for potential loss to follow-up.

The sample size calculation used the following formula for cluster-randomized trials:

$$n = 2 \cdot (Z_{\alpha/2} + Z_{\beta})^2 \cdot p \cdot (1-p) \cdot DE / (p_1 - p_2)^2$$

Where:

- $Z_{\alpha/2} = 1.96$  (for a 5% significance level).
- $Z_{\beta} = 0.84$  (for 80% power).
- $p$  = overall event rate (T2DM incidence in the control group).
- $p_1$  = event rate in the control group.
- $p_2$  = event rate in the intervention group (50% reduction).
- $DE$  = design effect, calculated as  $1 + (n-1) \cdot \rho$ , where  $\rho = 0.05$  (ICC).

*Assumptions:*

- The 5-year cumulative incidence of T2DM in Bangladesh was 16.4 per 1,000 person-years [34].
- A 50% reduction in T2DM incidence in the intervention group was assumed, based on previous trials.
- The design effect (DE) was calculated as 6.1, accounting for clustering within mosques.

*Calculation:*

1. Number of Participants per Arm:
  - Based on the formula and assumptions, 412 participants per arm were required to detect a 50% reduction in T2DM incidence with 80% power and a 5% significance level.
2. Total Sample Size:
  - To account for a 50% loss to follow-up, the total sample size was increased to 824 participants (412 in the intervention group and 412 in the control group).
3. Number of Clusters:
  - Participants were recruited from eight mosques, with approximately 103 participants per mosque.

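### Protocol section 10.6: 412 per arm does not follow from the printed formula with design effect 6.1, and the stated 80% power is not reached at any incidence the documents support

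*Combined protocol and SAP*

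**What the plan says.** Section 10.6 of the protocol gives a two-proportion formula multiplied by a design effect. Its inputs are Z = 1.96 and 0.84, an ICC of 0.05, and these assumptions:

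- Effect: "A 50% reduction in T2DM incidence in the intervention group was assumed, based on previous trials".
- Incidence: "The 5-year cumulative incidence of T2DM in Bangladesh was 16.4 per 1,000 person-years".
- Clustering: "The design effect (DE) was calculated as 6.1, accounting for clustering within mosques".

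The variance term p is described as "overall event rate (T2DM incidence in the control group", and DE is written as 1 + (n − 1)ρ. No numerical value is assigned to p1 or p2. The section then concludes: "Based on the formula and assumptions, 412 participants per arm were required to detect a 50% reduction in T2DM incidence with 80% power". It says the total was raised to 824 for 50% loss to follow-up, which is again 412 per arm, from eight mosques of about 103.

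The primary outcome (section 9.1) is cumulative incidence at 12 months. SAP section 4 gives a different basis: 12% control incidence, a 7-point absolute reduction, and an ICC of 0.041. The SAP describes itself as written after data collection, and is dated 20 August 2023.

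**The concern.** The protocol presents 412 per arm as the output of a named formula and listed assumptions, so the claim can be tested by substitution. It fails by a wide margin. A reader of the trial report would take 80% power for a halving as a property of the design. A non-significant result could then be read as evidence against the intervention when the design had little chance of detecting the planned effect. A significant result could be presented as coming from an adequately powered trial.

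**Working it through.** **Design effect.** 1 + (103 − 1) × 0.05 = 6.1. This reproduces, so the n inside DE must be participants per mosque (call it m), not the n the formula solves for.

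**Sample size.** The printed formula is n = 2(1.96 + 0.84)² p(1 − p) DE / (p1 − p2)². With p2 = p1/2 and p = p1 as printed, it reduces to

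n = 8 × 7.84 × 6.1 × (1 − p1)/p1 = 382.592 × (1 − p1)/p1.

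The control risk has to be inferred. As a 12-month risk, 16.4 per 1,000 person-years is 1.64%. Over five years it is 5 × 1.64% = 8.2%. Reading it as 16.4% contradicts the printed unit and is included only as the most generous case. The 12% is from SAP section 4, here halved.

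| Control risk | n per arm, p = control rate | n per arm, p = mean of arms |
|---|---|---|
| 1.64% | 22,946 | 17,281 |
| 8.2% | 4,283 | 3,284 |
| 12% | 2,806 | 2,176 |
| 16.4% | 1,950 | 1,534 |

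None is near 412. Solving 382.592(1 − p1)/p1 = 412 gives p1 = 382.592/(412 + 382.592) = 0.48. A 48% control risk appears nowhere in the documents.

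**Why these are not enrolment targets.** The table holds DE at 6.1, but with four mosques per arm DE grows with m. Effective size per arm is 4m/[1 + (m − 1) × 0.05], which cannot exceed 4/0.05 = 80. Without clustering, the formula with averaged p already needs 251.5 per arm at 16.4% (1,534/6.1). Enlarging the same eight mosques therefore could not reach 80% power at any of these rates.

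**Power at 412 per arm, no loss.** Effective size is 412/6.1 = 67.5. Let d = (p1 − p2)/√[2p(1 − p)/67.5]. Two-sided power is Φ(d − 1.96) + Φ(−d − 1.96).

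| Control vs intervention | d (p = control; p = mean) | Power |
|---|---|---|
| 1.64% vs 0.82% | 0.375; 0.432 | 6.6%; 7.2% |
| 8.2% vs 4.1% | 0.868; 0.992 | 14%; 17% |
| 12% vs 6% | 1.073; 1.218 | 19%; 23% |
| 16.4% vs 8.2% | 1.287; 1.451 | 25%; 31% |

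Both tails are counted; at 1.64% the favourable tail alone is about 6%.

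**The SAP's 12% vs 5%.** The mean of the arms is 0.085.

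- ICC 0.05: DE = 6.1, d = 0.07/√[2 × 0.085 × 0.915/67.5] = 1.459, power 31%.
- ICC 0.041: DE = 1 + 102 × 0.041 = 5.182, effective size 79.5, d = 1.583, power 35% (36% with arm-specific variances).

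Setting p to the control rate lowers these to 24% (d = 1.252) and 27% (d = 1.358).

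**The case against.** **The control risk is never stated.** This is correct, and it limits what can be claimed. The section gives one figure with mismatched labels, for Bangladesh, while the trial enrols people with prediabetes and a risk score of at least 9. A reader might infer that the trial needed about 23,000 per arm, or that its true power was about 7%. The documents do not support either: both depend on converting 16.4 per 1,000 person-years to a 12-month risk in this population, which the protocol does not do. What stands is that every reading misses 412.

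**Another calculation might lie behind 412.** Near matches exist, but only if the design effect is dropped. The two-sided, continuity-corrected size for 16.4% vs 8.2% is 274.5 per arm, and 274.5 × 1.5 = 411.8. A one-sided calculation at 8.2% with averaged p and no design effect gives 424. The SAP's 12% vs 5%, treated like the first, gives about 414. Several unrelated routes land close, so a reader should not infer that any of them is the source. All omit the 6.1 that the section says was applied. For the same reason it is not established whether 412 already contains a loss allowance. The power figures above assume no loss; any loss lowers them.

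**The SAP has its own basis.** It was written after data collection and is not the stated source of 412. On its inputs, 412 per arm still falls far short of 80%.

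**The formula faults are minor.** Agreed. Reusing n inside DE is a notation slip, since 6.1 is right for 103 per mosque. Using the control rate for p gives a larger n. Neither explains 412.

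**Conclusion.** The point holds in this form: with the printed Z values and DE of 6.1, no reading of the incidence gives 412 per arm. The formula returns 4.7 to 56 times that number with p as printed (1,950/412 to 22,946/412), or 3.7 to 42 times with averaged p. The lower end of each range rests on misreading the rate as 16.4%.

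At 412 per arm, power for a halving runs from about 7% to 31% across control risks of 1.64% to 16.4%. The SAP's larger assumed effect gives at most about 36%. The shortfall from 80% is therefore at least about 44 points. These figures assume equal mosques of 103, the stated ICCs, no loss to follow-up and a normal approximation, which is optimistic with only eight clusters.

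The failure of the arithmetic is certain. The trial's actual power is not, because it depends on a 12-month control incidence that the protocol does not give.

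**What to change.** Data collection is complete, so correct the record rather than the design.

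- Annotate section 10.6, and state in the SAP and report, that 412 per arm does not follow from the printed formula and that the claim of 80% power is withdrawn. Do not assert an origin for 412.
- Describe 824 as the size set by eight mosques of about 103.
- Write DE as 1 + (m − 1)ρ with m = participants per mosque, and set p = (p1 + p2)/2.
- Print a short table of power at 412 per arm for 12-month control incidences of 1.64%, 8.2%, 12% (including the SAP's 12% vs 5%) and 16.4%. Label where each incidence comes from.
- Interpret the primary result by its cluster-adjusted confidence interval.

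The cost is some rewording and a much less favourable stated power. Enrolment and data collection do not change.

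### As printed, the 50% allowance for loss to follow-up adds nothing: 412 per arm is both the number required before loss and the number after the increase for loss

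*Combined protocol and SAP*

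**What the plan says.** Protocol section 10.6 lists among its key parameters "Dropout Rate: 50% to account for potential loss to follow-up". The calculation then runs in three steps.

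- Step 1, labelled as the number per arm: "412 participants per arm were required to detect a 50% reduction in T2DM incidence with 80% power and a 5% significance level".
- Step 2, the total: "To account for a 50% loss to follow-up, the total sample size was increased to 824 participants", broken down as "412 in the intervention group and 412 in the control group".
- Step 3: eight mosques with about 103 participants each.

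The same section states: "The design effect (DE) was calculated as 6.1, accounting for clustering within mosques". Its formula for the design effect is one plus (cluster size minus one) times the ICC, with an ICC of 0.05.

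Elsewhere, protocol section 10.7 allocates 824 participants 1:1, and section 10.1 sets a recruitment ceiling of 108 per mosque. SAP section 4 gives another basis for the sample size (12% control incidence, a 7-point absolute reduction, ICC 0.041) and states no allowance for loss. SAP section 10, on deviations, does not mention the change of basis.

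**The concern.** An allowance for loss has to make the enrolled number larger than the evaluable number. Here the two are the same, so the step that claims to protect against loss changes nothing. A reader of section 10.6 would conclude that the trial keeps its stated power even if half the participants are lost. As printed, the plan does not have that property. The statement concerns the primary outcome, and it would be relied on by anyone judging how well the design stands up to missing 12-month glucose results.

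**Working it through.** **Inputs.** All are from protocol section 10.6 unless noted: 412 per arm required; 50% loss; 824 in total after the increase; 8 mosques; about 103 per mosque; ICC 0.05; z-values 1.96 and 0.84; a halving of the event rate; ceiling of 108 per mosque (section 10.1).

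**1. The loss step.**
- Before loss: 2 × 412 = 824.
- After the stated increase: 412 + 412 = 824.
- Factor applied: 824/824 = 1.00. Factor needed for 50% loss: 1/(1 − 0.5) = 2.00.
- With the needed factor: 412/0.5 = 824 per arm, 1,648 in total.
- Even the common mistake of multiplying by 1.5 gives 618 per arm, 1,236 in total. Neither matches the plan.

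**2. Is a reserve held elsewhere?** 8 × 103 = 824, the number allocated. The ceiling gives 8 × 108 = 864, of which half is 432 in total, or 216 per arm. There is no reserve of the size needed.

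**3. Could 412 be the total?** 412/0.5 = 824 exactly, so 206 per arm before loss would make step 2 correct and step 1 wrong. The formula does not settle it. With the stated design effect of 6.1 it gives the following numbers per arm. The control rate is shown under three readings, because the protocol labels 16.4 per 1,000 person-years as a 5-year cumulative incidence.

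| Control rate | p = control rate | p = mean of the two rates |
|---|---|---|
| 1.64% (one year) | 22,947 | 17,282 |
| 8.2% (five years) | 4,284 | 3,285 |
| 16.4% (read as a percentage) | 1,951 | 1,535 |

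Neither 412 nor 206 appears. This is why 1,648 only illustrates the missing step.

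**4. Power at 50% loss, conditional on the protocol's claim.** Assume, without being able to reproduce it, that 412 per arm at a design effect of 6.1 gives 80% power.
- Design effect as planned: 1 + (103 − 1) × 0.05 = 6.1. Effective number per arm: 412/6.1 = 67.5.
- After 50% loss: 206 per arm and 51.5 per mosque. Design effect: 1 + (51.5 − 1) × 0.05 = 3.525. Effective number: 206/3.525 = 58.4.
- Check at full follow-up: Φ(2.80 − 1.96) = Φ(0.84) = 0.80.
- After loss: Φ(2.80 × √(58.4/67.5) − 1.96) = Φ(0.644) = 0.74.

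This counts every lost participant as contributing nothing.

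**5. Loss reported in the SAP.** Section 4 gives a final sample of 799 after 25 exclusions: 799 + 25 = 824, and 25/824 = 3.0%. Section 5 gives 10 participants with no post-baseline data.

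**The case against.** The strongest reply is that this is a slip of labelling. Step 2 speaks of the total being increased to 824, which reads naturally as an increase from a total of 412. That possibility stands, and the formula cannot exclude it, since it supports 412 per arm no better than 206. It does not rescue the text: step 1 says per arm both in its label and in its sentence, so one of the two steps is wrong on either reading.

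A second reply is that lost participants are not worthless. Protocol section 12 censors them at last follow-up, and glucose is tested at 4 months, so those lost after that visit still contribute to the log-rank and Cox analyses. This also stands. The 74% is a lower figure on its own premise, and censored follow-up could recover part of the difference.

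Four stronger readings are tempting, and the documents do not support them.

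- A reader might hold the design effect at 6.1 after loss and get 206/6.1 = 33.8 effective per arm and power of about 51%. The protocol's own formula makes the design effect fall with cluster size, so this scenario is not coherent with eight mosques at half size.
- A reader might infer that 824 does give 80% power if follow-up is complete. On the protocol's inputs with a design effect of 6.1, power at 412 per arm is about 6%, 17% or 30% for control rates of 1.64%, 8.2% or 16.4%. That is a separate and larger problem.
- A reader might take the 6.1, computed at 103 per mosque, as proof that no loss was allowed for. A design effect at enrolled cluster size is compatible with a separate inflation step, so it proves nothing either way.
- A reader might say that the SAP dropped the allowance. As printed, there was none to drop. The SAP replaced the whole basis of the calculation.

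**Conclusion.** The point holds as an internal contradiction in protocol section 10.6. As printed, 412 per arm (824 in total) is the number before and after the increase for loss, and the stated allowance for 50% loss does not exist. If 412 was instead meant as the total, the error lies in step 1, and the resulting 206 per arm is not supported by the formula.

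The size is modest. Conditional on the unreproduced 80%, power at 50% loss is about 74%, a fall of about 6 points, with lost participants contributing nothing. The figure rests on equal loss across mosques and an ICC of 0.05. Nothing in the SAP suggests loss near 50%, though the flow chart is not shown and actual 12-month loss cannot be confirmed. The documents do not support a claim that loss to follow-up damaged the trial. What needs correcting is a design property that the protocol states and does not have.

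**What to change.** - The sponsor should state whether 412 is per arm or in total, and correct step 1 or step 2 of section 10.6 to match.
- If 412 per arm is the requirement, delete the claim that 824 accounts for 50% loss and say that 824 contains no allowance for loss.
- If 412 is the total, correct the per-arm label in step 1 and show how 206 per arm was obtained.
- Label any power quoted at 50% loss as conditional on the protocol's claim for 412 per arm at a design effect of 6.1. Give it as about 74% with the design effect recomputed to about 3.5, and note that censored follow-up may recover part of the loss.
- In SAP section 10, record that the sample-size basis in SAP section 4 differs from the protocol's and states no allowance for loss.

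The cost is wording only: no enrolment, data or analysis changes. The drawback for the sponsor is that a stated protection has to be withdrawn or re-explained.
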